### Activity performance domain

#### Assisting Hand Assessment (AHA)

The AHA is a Rasch analysed measure that evaluates how a child with a unilateral impairment (congenital hemiplegia or obstetric brachial plexus palsy) effectively makes use of his/her impaired UL in bimanual tasks [127]. The assessment is videotaped and 22 items are scored on a four point rating scale, with a range of possible raw scores of 22 to 88. Raw scores will be converted to interval level AHA units (logits- log odds probability units on a scale of 0 to 100), as recommended by test developers as the preferred method of reporting and measuring change [128]. Depending on the age of the child and in accordance with recommendations from test developers, one of the three versions of the AHA will be used (the small kids, school kids or adolescent version). The small kids and school kids versions have high test re-test reliability (ICC = 0.99 and 0.98 respectively) and reliability between the two forms is very high (ICC = 0.99). Reliability between the school kids and Ice Rocks (adolescent version) has not yet been reported, however the adolescent version will be used in this study for youth over the age of 12 years, as the school kids version is not valid nor age appropriate for this population. The AHA has been shown to be responsive to change due to UL interventions [103, 129, 130]. The MDC is estimated as five AHA units. Although the AHA is not validated in children with an ABI, it is expected that they will perform similarly to children with a unilateral impairment. In accordance with test recommendations, all therapists administering the AHA will have undergone standardised training and certification [127] and will be scored by one certified rater masked to group allocation and order of assessment.

#### Habitual Physical Activity (HPA)

HPA will be measured using ActiGraph® GT3X+ triaxial accelerometer (Shalimar, FL). The ActiGraph measures and records time varying accelerations of the trunk that ranges in magnitude from ± 6g. The ActiGraph accelerometer is a valid and reliable measure of ambulatory physical activity in children and adolescents with CP [57, 131]. ActiGraph-based estimates of Metabolic Equivalents (METS) is a valid method to differentiate between varying intensities of walking (slow, comfortable and brisk paced) in children and adolescents with CP using previously published cut points for TDC [131]. The ActiGraph has good to excellent reliability with stepping tasks (ICC = 0.66), light and moderate walking (ICC = 0.8) and vigorous walking (ICC = 0.7) in independently ambulant children and adolescents (aged 8 to 16 years) with CP [57]. In community dwelling adults with an ABI, ActiGraph-based estimates when compared to portable indirect calorimetry (Cosmed K4b^2^) as a criterion measure, provided a valid index of activity across different levels of walking intensities [132]. It is estimated that between four and five days of monitoring are required to reliably estimate daily physical activity in TDC [133]. Both weekdays and weekends will be included in the monitoring period due to marked differences in physical activity behaviour.

ActiGraphs will be fitted during assessment (on the dominant hip) and worn during waking hours for four days following assessment and training days. After four days it will be returned by courier for data extraction and analysis using the manufacturers ActiLife software. An activity log completed by the parents/guardians coupled with an ActiGraph to validate the ActiGraph accelerations against reported wear time will be given. Raw acceleration data will be considered for analysis where accelerations are recorded for >4h per day on at least one weekend and one weekday.

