### Design

This study utilises a matched-pairs, randomised waitlist controlled trial (see Fig. 1 for CONSORT flow chart). A matched pairs design was chosen to minimise the risk of baseline between-group differences. A waitlist design ensures that all participants have access to this novel intervention and will facilitate recruitment into the study. Within each pair, each participant will be randomised into either:*Immediate intervention group:* Families return home with Mitii™ equipment and commence training immediately for 20 weeks and then Mitii™ is withdrawn; or*Waitlist delayed intervention (control) group:* Families continue care as usual for 20 weeks, return to Brisbane for a one day re-assessment and then return home with Mitii™ equipment to commence training for 20 weeks. Care as usual includes any therapies (for example, occupational therapy and physiotherapy) usually provided by public or private services and visits to their treating paediatrician or general practitioner. Information about each participant’s usual care during the study period will be gathered using a general study questionnaire. After re-assessment the participants (and their family) will receive the Mitii™ introduction and equipment ready to commence training.

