### Study procedure

To account for children’s varying abilities to attend and concentrate and, to mitigate fatigue the following scheduling strategies will be used to maximise data integrity during baseline and follow up assessments. Families will be contacted prior to baseline assessments to ascertain whether they feel their child will need one or two days to complete assessments. All participants will attend The University of Queensland, St Lucia campus for all assessments, minimising travel. Neuropsychological testing will be scheduled first as this requires most attention and concentration by participants. Regular breaks will be scheduled for participants between assessments as necessary at baseline and follow-up appointments. All primary outcome clinical assessments will be performed prior to Magnetic Resonance Imaging (MRI). Extra time will be allocated at the start and end of each day to manage any unforeseen complications which may arise (e.g. travel/time delays and fatigue issues). Participants in the immediate intervention group will spend an additional day for Mitii™ training and return home with Mitii™ equipment to begin the 20 weeks intervention. After baseline assessments (T0), the waitlist group will continue care as usual for 20 weeks. All participants will then return to The University of Queensland after 20 weeks for a one to two day re-assessment (T1). The waitlist group will spend an additional day for Mitii™ training before returning home with equipment to commence the intervention. For each participant data will be collected at Baseline (T0). The immediate intervention group will have follow up assessments conducted immediately post-training at 20 weeks (T1) and retention at 40 weeks post-baseline assessments (T2). The waitlist group will have a second baseline assessment at 20 weeks (T1), post-intervention at 40 weeks (T2) and retention of effects at 60 weeks post-baseline assessments (T3).

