### Statistical analysis

Analysis will follow standard principles for RCTs. Primary and secondary outcomes will be assessed using two-group comparisons on all participants with evaluable data at 20 week follow-up assessments on an intention-to-treat basis. Statistical significance will be set at *p* < 0.05 for primary outcomes. Statistical significance for secondary outcomes will be defined separately for each suite of analyses prior to analyses being undertaken. Each significance level will be set to account for both type I and type II error rates due to the number of multiple comparisons. Validity of results will be checked using baseline and general descriptive information available for all eligible families. This includes comparing the key characteristics of families who completed the study with those who enrolled in the study but did not complete, and those who did not enrol. The primary outcome measures immediately post-intervention at 20 weeks will be AMPS and rep_max_ of functional strength exercises. Outcomes between treatment groups will be compared at follow-up using linear regression models, where treatment group (intervention or waitlist) and baseline score will be entered in as main effects. Secondary analyses will compare the outcomes between groups for physical activity, participation (CASE and CASP) and QOL (domains of Kidscreen-52).

For reproducibility studies (AMPS, physical activity capacity and performance measures and attention and executive functioning measures), units of variance will be assessed using an analysis of variance (ANOVA) model with Bland Altman Plots with 95 % limits of agreement (LOA). Intra-class correlation coefficients (model: 2-way mixed effects with absolute agreement) and 95 % confidence intervals will be calculated and interpreted as greater than 0.75 as excellent correlation, between 0.4 and 0.75 as adequate and less than 0.40, poor correlation [154]. The SEM will be calculated using [155]:$$ SEM= Standard\  Deviation\ (SD) \times \sqrt{\Big(1-ICC}\Big) $$

The MDC will be calculated using [155]:$$ MDC=SEM \times 1.96 \times \sqrt{2} $$

For attention and executive functioning measures, reliable change indexes (RCI) will be calculated using [156]:$$ RCI=\left( retestscore - initialscore\right)\div \left( standard\  error\  of\  difference,\  SDiff\right) $$

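### Activity monitors are worn after the visit, so the immediate arm's baseline window and the waitlist arm's 20-week window both fall after Mitii has been handed over

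*Protocol article*

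**What the plan says.** **Wear window.** Under Habitual Physical Activity (HPA), the monitor is fitted on the dominant hip during assessment and "worn during waking hours for four days following assessment and training days". The window then closes: "After four days it will be returned by courier for data extraction and analysis".

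**Immediate arm.** Under Study procedure, at baseline (T0) these children "will spend an additional day for Mitii™ training and return home with Mitii™ equipment to begin the 20 weeks intervention". Under Design, they "commence training immediately for 20 weeks and then Mitii™ is withdrawn". Their 20-week assessment (T1) comes straight after the training period.

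**Waitlist arm.** After T0 they stay on usual care for 20 weeks. At T1, "The waitlist group will spend an additional day for Mitii™ training before returning home with equipment to commence the intervention". Design agrees: after re-assessment, families "then return home with Mitii™ equipment to commence training for 20 weeks".

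**Use of the data.** Greater habitual activity with Mitii than with usual care is a secondary hypothesis. The Statistical analysis section makes two-group comparisons at 20 weeks by linear regression on treatment group and baseline score, and states that "Secondary analyses will compare the outcomes between groups for physical activity".

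**The concern.** A 20-week comparison of Mitii with usual care needs a control measurement taken under usual care and a baseline taken before either arm has received Mitii. The wear window follows the Mitii training day, so neither condition is protected. The control measurement at T1 begins once the usual-care period has ended. The baseline in the immediate arm begins once those children have been sent home to train, and the regression then adjusts for that value.

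The Background says that no study has evaluated the effect of any intervention on objectively measured activity in children with acquired brain injury. This trial's estimate would therefore be the first of its kind, and a bias built into the measurement schedule could not be removed by the planned baseline adjustment.

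**Working it through.** **Step 1. Line up the windows.**

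| Wear window | Immediate arm | Waitlist arm |
|---|---|---|
| Four days after T0 visit | Sent home to start Mitii | Usual care |
| Four days after T1 visit | Mitii withdrawn | Sent home to start Mitii |

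No statement in the article holds back the first session until the monitor is returned, and none places wear before the visit.

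**Step 2. Reproduce the stated dose.** The Abstract gives 30 min a day, six days a week, for 20 weeks: 20 x 6 x 30 / 60 = 60 h, as stated. The article gives no sample size, SD or expected effect for the accelerometer outcome, so there is no planned figure for that outcome to check.

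**Step 3. Contamination per window.** The Mitii intervention section puts the gross-motor share of each session at about 40 %. Averaged over where the rest day falls:

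- Sessions in four days: 4 x 6/7 = 3.4.
- Gross-motor time: m = 0.40 x 30 x 6/7 = 10.3 min/day.

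This is an upper figure for the gross-motor share. It assumes that training starts on the first wear day, that every session is done, that session time adds to other activity, and that the monitor registers all of it. The lower end is 0, if the first session falls after the monitor is returned or if sessions only replace other activity.

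**Step 4. Effect on the adjusted comparison.** Let d be the difference (immediate minus waitlist) that uncontaminated windows would give, and b the regression slope of T1 on T0. Take the same m in both affected windows.

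- Observed T1 difference: d - m, because the waitlist arm is raised.
- Observed T0 difference: +m, because the immediate arm is raised.
- Adjusted difference: (d - m) - b x m = d - m(1 + b).

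The slope is not given, so 0.3 to 0.7 is assumed:

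| b | Shift at m = 10.3 (min/day) | Shift at 50 % adherence (min/day) |
|---|---|---|
| 0.3 | -13.4 | -6.7 |
| 0.5 | -15.4 | -7.7 |
| 0.7 | -17.5 | -8.7 |

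With m = 0 the shift is 0. The two errors have the same sign, so adjusting for baseline adds to the bias instead of reducing it.

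**The case against.** **The date of the first session is not given.** The Mitii intervention section has the three trainers build each child's program after the family has returned home. A lag of some days would remove much of the overlap, and a lag of four days or more would remove all of it. This stands, and it is why the range starts at 0. It does not clear the schedule. Design has the immediate arm start at once, no lag is stated, and the waitlist T1 window would still lie after the scheduled usual-care period.

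**Measuring the immediate arm after withdrawal is defensible.** The target is habitual activity, and wear after withdrawal asks whether everyday activity rose without counting the prescribed exercise. This also stands. A reader might infer that the absence of Mitii-period data in that arm is itself an error, but the documents do not support that. The defect lies in the other two windows.

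**Sessions may not add fully to measured activity.** The Background reports that the two larger cerebral palsy studies did not reach the prescribed dose, although adherence in the smaller pilot was high. The HPA section gives its lowest reliability for stepping tasks (ICC 0.66), and the modules include sit-to-stand work. These points lower the size. Against them, the planned ActiGraph validation includes a 15 min Mitii session, so the investigators do treat it as activity worth measuring with the device.

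**It is one secondary outcome among many.** This is correct and limits the severity.

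**Conclusion.** The point holds in a limited form. As scheduled, the wear window does not protect the immediate arm's baseline or the waitlist arm's 20-week value from Mitii. If sessions add measured activity, both errors bias the comparison against Mitii. The illustrative size is 0 to about 10 min/day of gross-motor activity per affected window, and an adjusted shift from 0 to about -13 to -17.5 min/day at assumed slopes of 0.3 to 0.7. A start lag, partial adherence or substitution makes it smaller.

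Three stronger readings are not supported:

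- A reader might infer that both affected windows are certainly on treatment throughout. The day of the first session is not stated.
- A reader might count 12 min of gross-motor work every day, giving 12 x 1.3 = 15.6 to 12 x 1.7 = 20.4 min/day, and set this against the 60 min guideline in the Background. Training is six days a week, and that guideline concerns moderate to vigorous activity, which gross-motor module time is not shown to be.
- A reader might conclude that the result would change sign. With no expected effect or SD for this outcome, that cannot be judged.

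Outcomes measured at the visits, including both primary outcomes, are taken before the waitlist training day and are unaffected. The sample size does not rest on activity. This should be fixed, but it does not threaten the trial's main conclusion.

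**What to change.** Change the HPA section so that, at T0 and T1 and in both arms, the monitor is couriered out and worn for the four days before the visit. T0 wear would then precede any Mitii training day, and the waitlist arm's T1 wear would fall within usual care. The window must still include a weekend day and a weekday, as that section requires.

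This change has a consequence that must be handled in the same edit. In the immediate arm, T1 wear would fall at the end of training and include prescribed sessions, up to the same 10.3 min/day of gross-motor time, which would favour Mitii mechanically. The section should state whether session time counts as habitual activity. The T1 comparison should be reported with and without session time, identified from the program's usage records (login frequency and time engaged, described under the Mitii intervention) and the parent activity log.

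The cost is outbound courier delivery (return by courier is already planned), an instruction sheet, and fitting at home instead of by staff, with some risk of incorrect placement. No extra visit is needed.

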#### Canadian Occupational Performance Measure (COPM)

The COPM will be used to measure self-perception of performance and satisfaction with performance of individualised occupational goals [54, 134]. One occupational therapist will administer the COPM with the child/adolescent and parent at the baseline assessment. Caregivers and children will identify areas of difficulty in everyday occupational performance and prioritise these on a scale of 1 to 10. Three to five priority goals will be identified and perceived level of performance and satisfaction with performance will be rated on a scale between 1 and 10 (1 indicates poor performance/low satisfaction and 10 indicates very good performance/high satisfaction). An average score for performance and satisfaction is calculated [93]. Ratings from caregivers will be used for children under the age of eight years of age, and ratings from children over eight years of age in collaboration with their caregiver will be reported. The COPM was designed for all ages and disability groups, has good evidence of construct, content and criterion validity and good test re-test reliability for performance and satisfaction scores (ICC 0.76–0.89) [134–136]. The COPM is responsive to change in paediatric clinical trials [137, 138]. A change of two points or greater has been reported as being clinically significant [54].

#### Physical capacity and performance test-retest reproducibility and validity

Participants will have the option to participate in test-retest reproducibility study of rep_max_ of functional strength exercises, 6MWT, HiMAT and TUG test over two days at the testing facility during baseline (for the immediate group) or 20 week follow-up assessments (for the waitlist group). Accuracy between hand-timed and videos scores during the HiMAT and TUG test will also be investigated. Testing will be performed in the same order by the same physiotherapist.

Participants will also have the option to participate in the validation for the ActiGraph accelerometer as a measure of physical activity intensity in children and adolescents with an ABI. To validate the ActiGraph accelerometer, participants will be asked to return for one assessment day after they have completed the primary end-point (20 week assessment) for the RCT. For the validity protocol, participants will be asked to rest for a 5–10 min period and then conduct selected light, moderate and vigorous assessment tasks, interspersed with 5–10 min rest periods in a standardised manner. To finish, they will complete a 15 min Mitii™ training program adjusted for their individual capacity. These tasks will be performed whilst wearing an ActiGraph accelerometer, heart rate monitor and a portable indirect calorimeter (MetaMax®). For test-retest reproducibility of the ActiGraph accelerometer, participants will rest for five minutes before conducting selected light, moderate and vigorous assessment tasks, interspersed with 5 min rest period in a standardised manner over the baseline assessment and training days.

#### MobQues47

Activity limitations will be measured using the MobQues.[59] The MobQues was originally designed to measure the mobility limitations a child with CP experiences in everyday life and to cover a broad range of severity of mobility limitations, as rated by their parents. Two versions of the MobQues are available; the MobQues47 and the MobQues28 with 47 and 28 mobility items, respectively. Response options for the MobQues are: Impossible without help (score 0), very difficult (score 1), somewhat difficult (score 2), slightly difficult (score 3) or not difficult at all (score 4). Total scores are calculated by adding up the item scores. Total item scores are then divided by the maximum possible score (i.e. 188 for MobQues47 and 112 for the MobQues28) and multiplied by 100 to obtain values on a scale of 0 to 100 (with lower scores representing more severe mobility limitations). For research purposes, the shorter version (MobQues28) is recommended as it has stronger psychometric properties (based on Rasch analysis) whereas; the MobQues47 can be used for clinical applications, to assess the child’s limitations in a wide variety of mobility activities [59]. Content validity has been demonstrated as 46 out of the 47 test questions related to ‘mobility’ according the definitions in the ICF. Construct validity was demonstrated as MobQues scores decreased with increasing GMFCS levels (*p* < 0.001). In a subgroup of 162 children, MobQues score was positively correlated to GMFM-66 (Mobques47, *r =* 0.75; MobQues28, *r =* 0.67, *p* < 0.001) [139]. Reliability has also been demonstrated. For inter-rater reliability, high ICC were found for the MobQues47 (ICC = 0.92) and MobQues28 (ICC = 0.87). The SEM was 7.8 and 8.9 respectively. Intra-rater was higher with ICC of 0.96–0.99 and lower SEM (3.5–4.9) for both versions of the test [59]. The English version has not yet been cross-validated therefore, the results demonstrated may differ slightly to that in an English speaking population. The MobQues47 will be collected at baseline (to allow cross-validation) and in follow-up assessments, the MobQues28 will be used (stronger psychometric properties). This questionnaire will be available for caregivers to fill out in either paper or online format.

### Participation domain

#### The Child and Adolescent Scale of Environment (CASE)

The CASE was initially developed as part of the Child and Family Follow-Up Survey (CFFS) to monitor outcomes and needs of children with an ABI (as informed by the ICF) [140]. The CASE consists of 18 items on a three point ordinal scale (no, little or big problem) that asks parents about the impact of problems experienced with physical, social and attitudinal environment features of the child’s home, social and community and those related to the quality and availability of services of assistance that the child receives or might need. The CASE can be administered in five minutes and no specialist training is needed to administer it. The CASE has reported evidence for test re-test reliability (ICC = 0.75), internal consistency (α = 0.84–0.91) and construct/discriminant validity. Higher CASE scores (greater extent of environmental problem) were significantly associated with lower scores on the Child Adolescent Scale of Participation (CASP, more restricted participation, r = −0.57, [141]; r = −0.43, [142]) and on the Paediatric Evaluation of Disability Index (PEDI, more limited functional skills) mobility (r = −0.28) and social function (r = −0.31) subscales [143]. This questionnaire will be available for parents and/or guardians to fill out in either paper or online format.

